### Outcome Measures

All outcome measures for AD patients will be done in 60-min session, pre and post intervention phase. The Reliable Change Index (RCI) will be used to minimize the practical effects, as described in the “Proposed Analysis” section.

#### Primary Outcome

The AD Assessment Scale, cognitive subscale (ADAS-Cog; Rosen et al., 1984), will be used to analyze the primary outcome. The ADAS-Cog consists of an 11-item cognitive subscale related to memory, orientation, visuo-spatial ability, language and ideational praxis. The main cognitive domains assess memory, language, praxis and understanding. The instrument has inter-rater reliability values ranging from 0.947 to 0.99 and test-retest values ranging from 0.59 to 0.92, and it is considered reliable for application to patients with AD. Scores range from 0 to 70, with higher scores reflecting more cognitive impairment.

#### Secondary Outcomes

##### The Neuropsychiatric Inventory Questionnaire (NPI-Q; Kaufer et al., 2000)

This instrument is completed by caregivers and provides information regarding 12 typical behavioral and psychological symptoms that may occur in patients with dementia. In this study, we used a severity rating (1 = mild, 2 = moderate, 3 = severe) for identified symptoms, deriving a severity score (range 0–36), with zero indicating no neuropsychiatric symptoms. The reliability and validity of this modified NPI score have previously been established.

##### The Cornell Scale for Depression in Dementia (CSDD; Alexopoulos et al., 1988)

This instrument is a 19-item clinician-administered instrument that uses patient and caregiver information to assess symptoms of affective disturbance in patients with dementia. It assesses mood-related signs, behavioral disturbances, physical signs, cyclic functions and ideational disturbances. Each item of the Cornell Scale for Depression in Dementia (CSDD) is evaluated on a three-point scale (0–2) that reflects symptom severity. Hence, the total score ranges from 0 to 38, with higher scores depicting greater depression. The reliability and validity of this CSDD score have been previously established.

##### The Disability Assessment for Dementia (DAD; Gélinas et al., 1999)

This instrument is an informant-based scale composed of 17 items pertaining to basic ADLs (hygiene, dressing, continence and eating) and 23 items pertaining to instrumental ADLs (meal preparation, telephoning, going on an outing, finance and correspondence, medications and leisure and housework). Each item is evaluated for initiation, planning and effective execution. To avoid bias toward certain activities (e.g., meal preparation), nonapplicable questions are omitted from the final score, and the score is reported as a percentage. The maximum total score is 100, with lower Disability Assessment for Dementia (DAD) scores denoting greater impairment. Basic ADL and instrumental ADL subscores are included in the analysis, in addition to total DAD scores (Bahia et al., 2010).

##### The Zarit Burden Interview (Zarit et al., 1985)

This instrument (22 items) is used to measure caregivers’ perceived burden in diverse domains (Zarit et al., 1985). The scale was validated for the Brazilian population (Taub et al., 2004), with acceptable internal reliability (Cronbach’s alpha), ranging from 0.77 to 0.88. The score responses range from 0 (never) to 4 (almost always) to prevent discrepancies with the original scale scores. Total scores range between 0 and 88 points, with higher scores reflecting higher caregiver burden.

Given the possibility of biases associated with this procedure, we perform the neuropsychological assessments on two consecutive days, respecting the limits of patients and their caregivers and offering them breaks for rest and hydration, whenever necessary.

##### Brain-Derived Neurotrophic Factor (BDNF)

Serum brain-derived neurotrophic factor (BDNF) levels will be measured with the BDNF Emax Immunoassay system kit (Promega, Madison, WI, USA), according to the manufacturer’s instructions. Blood samples will be collected and allowed to coagulate for 1 h at room temperature, followed by 1 h at 4°C. Serum will be separated by centrifugation at 2000 g for 10 min at 4°C, put in an aliquot and stored at −80°C until used in 0.2 ml tube strips.

### Ethics, Participant Consent and Study Registration

This study is being carried out in accordance with the recommendations of National Health Council with written informed consent from all subjects. All subjects will provide written informed consent in accordance with the Declaration of Helsinki. The protocol was approved by the Institutional Ethics Committee on Human Research. In case of inability to understand the instructions or due to the presence of anosognosia, both the participant and caregiver will sign the informed consent form. The study was approved by the *Brazil’s National Committee for Ethics in Research* (CAAE: 44388015.7.0000.5188) and publicly registered in the ClinicalTrials.gov database (NCT02772185). The trial protocol follows the SPIRIT (Standard Protocol Items: Recommendations for Interventional Trials) guidance for protocol reporting (Chan et al., 2013).

### Sample Size

The sample size was estimated based on previous studies that used paired tDCS groups in treating AD (Ferrucci et al., 2008; Boggio et al., 2012). The power calculations determining the number of participants in each group were made in relation to the expected change in ADAS-Cog because this instrument is commonly used in studies involving cognitive evaluation in these patients (Vellas et al., 2007; Balietti et al., 2017; Xiao et al., 2017).

The expected significant improvement is reaching 3.76 points in the mean, with an standard deviation (SD) of 1.32 points, according to Rabey et al. (2013). Therefore, a calculation considering the level of *p* < 0.05 and 90% power as significant suggests that at least 10 patients would be necessary in each group to detect whether the difference found matches the effect of the active or simulated treatment. Considering the application of tDCS in multiple areas, stimulation time and the possibility of sample losses throughout the study (dropout, inability to continue treatment, death), 25 patients per group will be included, totaling 100 participants.

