Accordingly, we propose that stimulating different brain regions specifically related to the neuropathology of AD along with repeated applications of 10-min tDCS in each session may be an option to achieve short- and long-term effects. However, at this time we have only just drawn up a study protocol and these hypotheses can only be tested in the main clinical trial that we aim to perform. In addition, no reports of factorial randomized clinical trials using with tDCS and cognitive intervention stimulating different cortical regions with a 10-min interval in each, and with follow-up for AD-related outcomes have been found to date.

In this way, we designed the Neurostimulation combined with Cognitive Intervention in AD (NeuroAD) clinical study, a phase II/III trial, to address the safety and efficacy of tDCS and cognitive intervention in the treatment of AD. Based on the aforementioned data, which suggest beneficial effects of both cognitive intervention and tDCS on patients with AD, we hypothesize that combining both treatments modulates cortical activity and improves the long-term clinical symptoms of patients, manifested as increased cognition and functional capacity and reduced affective and behavioral changes.

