The expected significant improvement is reaching 3.76 points in the mean ADAS-Cog, with a SD of 1.32 points, according to Rabey et al. (2013). Thus, we consider the difference of at least three points in the ADAS-Cog and in the pre- and post-treatment measures to be clinical improvement. All participants with clinical improvement will be considered as respondents.

In all steps, the primary and secondary outcomes assessments will be repeated. The pre-intervention measurement is planned to be performed in the week before the intervention starts and the post-intervention measurement is planned for the first week after the intervention.

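### The 10 per group for 90% power does not follow from 3.76 points and SD 1.32 (about 4 would do), and the paragraph does not say which between-group contrast is powered

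*Protocol article*

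**What the plan says.** The Sample Size section of the protocol article bases the calculation on earlier tDCS studies with paired groups and on the expected change in ADAS-Cog. Its inputs are: "The expected significant improvement is reaching 3.76 points in the mean, with an standard deviation (SD) of 1.32 points", taken from one cited study, and "a calculation considering the level of *p* < 0.05 and 90% power as significant". It concludes that this "suggests that at least 10 patients would be necessary in each group to detect whether the difference found matches the effect". The comparison meant is active against simulated treatment. The number is then raised to 25 per group, 100 in all, to allow for several stimulated areas, stimulation time and losses. No dropout rate, test, sidedness or control-arm change is given.

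Other sections bear on this:

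- Stepwise Procedures repeats 3.76 (SD 1.32) and derives a responder rule from it: "we consider the difference of at least three points in the ADAS-Cog and in the pre- and post-treatment measures to be clinical improvement". Proposed Analysis prints the SD as 1.33.
- Primary Outcome gives the ADAS-Cog range as 0 to 70 and "test-retest values ranging from 0.59 to 0.92", but no between-patient SD.
- Overview sets out four arms in a 2x2 layout. Proposed Analysis plans a split-plot ANOVA with Bonferroni post hoc comparisons where appropriate.
- The Introduction states the hypothesis: "we hypothesize that combining both treatments modulates cortical activity and improves the long-term clinical symptoms of patients". Anticipated Results expects the design to show whether the therapies should be used alone or together.

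**The concern.** This is the only power justification for the primary outcome, and its inputs and its answer do not match. Either the 10 came from inputs that are not printed, or the printed SD is not the one used.

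Two further gaps make the paragraph hard to use. First, 3.76 is described as an improvement, and Stepwise Procedures ties it to a pre-post criterion, yet the sample size is said to separate active from simulated treatment. Without a control-arm change, a pre-post gain is not a treatment difference. Proposed Analysis itself warns that repeated testing may improve scores. Second, a 2x2 trial supports main effects, pairwise comparisons and an interaction. These differ widely in precision, and the paragraph names none of them.

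Readers therefore cannot tell which effects 100 patients can detect. A null result for the combination could be read as evidence against it when the trial may have had little power for that contrast.

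**Working it through.** **Inputs from the protocol article.** Difference 3.76; SD 1.32; alpha 0.05 (taken as two-sided, since sidedness is not stated); power 90%; 25 per cell; test-retest r = 0.59 to 0.92.

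**Step 1: try to reproduce 10 per group.** d = 3.76/1.32 = 2.85.

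- Normal approximation: n = 2(1.960 + 1.282)²/2.85² = 2.6, so 3 per group.
- Exact two-sample t, noncentrality 3.76/(1.32·√(2/n)): power is 74% at n = 3, 91.5% at n = 4 and above 99.99% at n = 10. Answer: 4.
- Paired t, noncentrality 3.76/(1.32/√n): 71% at n = 3, 95% at n = 4. Answer: 4.
- Two-sample t with alpha 0.05/6: 81% at n = 5, 92% at n = 6. Answer: 6.
- Four-group ANOVA: 3 to 5, depending on the pattern of means.
- Interaction of 3.76 points, SE = 2·SD/√n per cell: 91% at n = 6. Answer: 6 per cell.
- A one-sided test gives no larger n, and SD 1.33 gives the same two-sample, paired and Bonferroni answers.

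No variant using 3.76 gives 10. Replacing 3.76 by the 3-point responder threshold gives 6 per group pairwise, or 9 per cell for an interaction. The latter comes closest but is not the calculation described.

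**Step 2: what would give 10?** Solving for exactly 90% power at n = 10 and 3.76 points gives SD 2.45 (two-sample) or 3.26 (paired).

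**Step 3: is an SD of change of 1.32 plausible?** With equal variances at both visits, SD_change = SD_between·√(2(1 − r)).

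- r = 0.92: √0.16 = 0.400, so SD_between = 1.32/0.400 = 3.3.
- r = 0.59: √0.82 = 0.906, so SD_between = 1.32/0.906 = 1.5.

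So 1.32 fits the stated reliability only if patients differ by an SD of about 1.5 to 3.3 points on a 0 to 70 scale.

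**Step 4: what 25 per cell delivers.** The documents give no between-patient SD. Assuming 6 to 8 points, SD_change runs from 6 × 0.400 = 2.4 to 8 × 0.906 = 7.2. Standard errors on the change score are SD·√(4/100) for a main effect (50 v 50), SD·√(2/25) for one pair, and SD·√(4/25) for the interaction. Power for a true 3.76-point effect, two-sided 0.05, before dropout:

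| Assumed SD of change | Main effect, 50 v 50 | Pair, 25 v 25 | Pair, Bonferroni for six | Interaction |
|---|---|---|---|---|
| 2.4 | >99.9% | >99.9% | 99.6% | 97% |
| 3 | >99.9% | 99% | 95% | 87% |
| 4 | 99.6% | 90% | 71% | 64% |
| 5 | 96% | 74% | 47% | 46% |
| 7.2 | 73% | 44% | 20% | 25% |

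The largest SD of change that still gives 90% power is about 5.7 (main effect), 4.0 (pair), 3.3 (six-pair Bonferroni) and 2.9 (interaction).

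**Step 5: the step from 10 to 25.** If it were all for loss, it would imply 1 − 10/25 = 60% dropout. The text gives other reasons as well, but assigns no number to any of them.

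**The case against.** The best defence is that the error does no harm. On the printed inputs, 10 per group already exceeds what is needed and 25 are enrolled. Six-pair Bonferroni and a 3.76-point interaction each need only 6 per cell. Even an interaction half that size (1.88 points) needs 22 per cell at SD 1.32. Every unfavourable power figure above rests on an assumed SD. This stands, and it rules out inferring from the mismatch that the trial is underpowered.

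A reader might also infer that the reliability figures contradict the SD. They do not. Reliability fixes the SD of change only together with a between-patient SD, which the article does not give, and entry limited to CDR 1 and MMSE above 18 narrows the spread. The implied 1.5 to 3.3 points looks small, but that is a judgement.

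Nor can it be said that 3.76 was certainly a within-arm change in its source, which is not at hand. What can be said is that the article describes it as a change and does not give the between-group difference.

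Finally, tDCS against placebo is among the stated aims, so a two-group comparison is not foreign to the trial. The hypothesis speaks of benefit from combining treatments without specifying an interaction test, and Bonferroni is planned only where appropriate, so six pairs is an illustration. All this is fair, but it leaves the powered contrast unnamed.

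The defence does not rescue the figure of 10. It is safe only if 1.32 is right, and the failure to reproduce 10 is one reason to doubt that.

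**Conclusion.** The figure of 10 per group is wrong as written. The printed inputs need about 4 (6 with six-pair Bonferroni), and 10 would need an SD of 2.45 or 3.26. This conclusion uses only the document's numbers. It is also established that the paragraph states no control-arm change and no target contrast.

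Whether 100 patients are enough is not settled by the document. Under the assumed SDs of change of 2.4 to 7.2, a main effect of 3.76 points has power from above 99.9% down to 73%, and an interaction of that size from 97% down to 25%. It would be too strong to say that pairwise and interaction contrasts lack 90% power unless the SD is very small: the limits of 4.0, 3.3 and 2.9 all lie inside the assumed range. The power figures treat the analysis as a comparison of change scores with a common SD and no dropout.

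**What to change.** Keep N = 100 and rewrite the Sample Size paragraph:

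1. Delete the statement that 10 per group is sufficient for 90% power.
2. State the between-group difference in ADAS-Cog change that is targeted, with the control-arm change assumed.
3. Give a justified SD of change with its source, use one value throughout (1.32 and 1.33 both appear), and state a dropout rate.
4. Say which contrast the 90% refers to. Report what 25 per cell delivers, after dropout, for each main effect (50 v 50), the pairwise comparisons and the interaction, over a range of SDs as in the table above.
5. State that, before dropout, 90% power for 3.76 points holds up to an SD of change of about 5.7 (main effect), 4.0 (pairwise), 3.3 (six-pair Bonferroni) and 2.9 (interaction).

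The cost is one paragraph and the work of finding a defensible SD, which the article does not supply. No patients are added and no analysis changes. The downside is that the stated power may become less favourable for pairwise and combined-therapy claims.

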#### Proposed Analysis

Intent-to-treat analysis will be used; that is, all participants will be included in the analysis, including those who drop out before completing the treatment. However, high or different rates of dropouts between the treatment arms may lead to biases. Thus, a sensitivity analysis will be performed with different assignment procedures to assess the value of the data. The best strategy resulting from the following methods will be chosen: last observation carried forward, complete case analysis, likelihood-based methods, or multiple imputation.

Descriptive statistics will be used to describe clinical and sociodemographic characteristics and the primarily and secondary outcomes of each group at the baseline. The groups will be compared by analysis of variance (ANOVA), for continuous variables, or the chi-square test, for categorical variables.

The primary outcome will be examined by split-plot ANOVA with one dependent variable (ADAS-Cog score) and two independent variables, namely, one intra-group variable and one inter-group variable. The within-subject variable will include time (baseline, post-treatment and 12-month follow-up), and the effects of the treatment condition (active or placebo tDCS; active or placebo cognitive intervention) will be examined as a between-groups variable. *Post hoc* comparisons using Bonferroni correction will be performed where appropriate. Finally, the effect sizes regarding inter-group comparisons will be calculated using the eta squared (*η*^2^), and effect sizes regarding intra-group comparisons will be calculated by means of Cohen’s d using Hedges’ correction (Fritz et al., 2012), adopting the significance level of *p* < 0.05. For all variables of the secondary outcomes, the same analysis strategy will be used. Non-parametric tests will be performed if some of the outcomes do not meet the conditions necessary for parametric analysis.

Considering the different evaluations with the same cognitive tests throughout the clinical trial, the improvement in the performance of these tests may result from practice and not from the intervention applied (Chelune, 2010; Goldberg et al., 2015). A RCI will be used; it serves to assess whether the changes identified comparing pre- and post-intervention data can be attributed to the procedures used or are mere oscillations, artifacts, or measurement errors (Jacobson and Truax, 1991) resulting from repeated practice effects (Chelune et al., 1993). The RCI, correcting for practice effects and using the Iverson’s standard error of the difference will be calculated based on the Duff’s (2012) formulae.

The follow-up analysis will calculate the primary outcome (i.e., a decline in cognitive state). As proposed in Phase 1, the same cutoff will be used to classify clinical improvement (3.76 points in the mean, with an SD of 1.33 points in the ADAS-cog). The primary outcome measure will be calculated considering the differences between clinical improvement and clinical relapse (or censored if relapse did not occur). Kaplan-Meier survival analysis will be used to calculate this outcome. To investigate interactions of risk factors, the following variables will be observed: demographics characteristics (age, gender, level of education), clinical condition (duration of illness, comorbidities and neuropsychiatric states) and “methodological” variables (Phase 1 group and crossover). The hazard ratio will be estimated using the Cox proportional hazards (to each predictor variable or covariate)”

Regarding safety, adverse effects will be analyzed in terms of the ratio in each group and period (before and after treatment) and analyzed using Fisher’s exact test. Multivariate regression will be used to identify predictors of response. The outcome variables will be tDCS and cognitive intervention, and the predictors will be age, gender, comorbidities and use of medication.

The effectiveness of the blinding will be analyzed by using the chi-square test, comparing the ratio between errors and correct responses. Furthermore, these tests will be compared between patients with clinical response and those who failed to improve.

Multivariate imputation by chained equations (MICE, the R Foundation for Statistical Computing, Vienna, Austria; van Buuren and Groothuis-Oudshoon, 2011) and the Statistical Package for Social Sciences (SPSS) version 21 (IBM Corp. Released, 2011, IBM^®^, SPSS Statistics version 21) software will be used.

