## Abstract

Despite advances in the treatment of Alzheimer’s disease (AD), there is currently no prospect of a cure, and evidence shows that multifactorial interventions can benefit patients. A promising therapeutic alternative is the use of transcranial direct current stimulation (tDCS) simultaneously with cognitive intervention. The combination of these non-pharmacological techniques is apparently a safe and accessible approach. This study protocol aims to compare the efficacy of tDCS and cognitive intervention in a double-blind, randomized and factorial clinical trial. One hundred participants diagnosed with mild-stage AD will be randomized to receive both tDCS and cognitive intervention, tDCS, cognitive intervention, or placebo. The treatment will last 8 weeks, with a 12-month follow-up. The primary outcome will be the improvement of global cognitive functions, evaluated by the AD Assessment Scale, cognitive subscale (ADAS-Cog). The secondary outcomes will include measures of functional, affective, and behavioral components, as well as a neurophysiological marker (Brain-derived neurotrophic factor, BDNF). This study will enable us to assess, both in the short and long term, whether tDCS is more effective than the placebo and to examine the effects of combined therapy (tDCS and cognitive intervention) and isolated treatments (tDCS vs. cognitive intervention) on patients with AD.

**Clinical Trial Registration**: www.ClinicalTrials.gov, identifier NCT02772185—May 5, 2016.

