## Materials and Equipment

### Overview

NeuroAD is a factorial, placebo-controlled, double-blind and randomized clinical trial in which 100 patients at the mild stage of AD are randomly assigned to four groups: 1—active tDCS and active cognitive intervention; 2—sham tDCS and active cognitive intervention; 3—active tDCS and placebo cognitive intervention; and 4—sham tDCS and placebo cognitive intervention. All of the patients will be subjected to tDCS and cognitive intervention applied for 24 workdays. At the end of the trial, patients who received active tDCS and achieved clinical response will be invited to maintain tDCS bimonthly for 12 months, as part of a long-term study of tDCS for AD; those who did receive sham tDCS and did not respond will be offered 24 open-label daily sessions of tDCS (crossover study); finally, those who showed response with cognitive intervention (real or placebo) and sham tDCS will be referred to other neuropsychological centers specialized in treating dementias in our Institution.

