## Anticipated Results

Considering there is a serious lack of factorial designs for clinical trials in non-invasive cerebral stimulation for AD patients, we aim to ameliorate that situation by observing the effect size and clinical effectiveness of each procedure, not only comparing this intervention against a sham (which could prove the efficacy, but not the clinical effectiveness), but also against a cognitive intervention. Further, we hope to broaden the treatment scope, promoting improvement in cognitive and functional aspects by stimulating different cortical regions, in addition to memory. Therefore, our study may generate key results for clinical practice and patient management throughout the disease.

Then, to the best of our knowledge, our study may be the first to apply a factorial design in non-invasive cerebral stimulation for AD patients, and not only comparing this intervention against a sham (which could prove the efficacy, but not the clinical effectiveness), but also against a cognitive intervention. Next, this factorial design will be able to observe the effect size and clinical effectiveness of each procedure, and will also be able to elucidate whether it would actually be feasible to apply the therapies alone or in combination. Further, we hope to broaden the treatment scope, promoting improvement in cognitive and functional aspects by stimulating different cortical regions, in addition to memory. Therefore, our study may generate key results for clinical practice and patient management throughout the disease.

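### The primary model for a 2x2 factorial trial has a single between-groups variable, and no tDCS, cognitive-intervention or interaction test is specified

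*Protocol article*

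**What the plan says.** The Overview section states that "NeuroAD is a factorial, placebo-controlled, double-blind and randomized clinical trial" and lists the four cells formed by crossing active or sham tDCS with active or placebo cognitive intervention, for 100 patients in all. The Abstract gives among its aims "to examine the effects of combined therapy (tDCS and cognitive intervention) and isolated treatments (tDCS vs. cognitive intervention) on patients with AD". The Anticipated Results section expects that "this factorial design will be able to observe the effect size and clinical effectiveness of each procedure", and that the trial will show whether to use the therapies singly or together.

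The Proposed Analysis section sets the primary analysis as a split-plot ANOVA of the ADAS-Cog score with "two independent variables, namely, one intra-group variable and one inter-group variable". The within-subject variable is time, at three points. On the other variable the text says that "the effects of the treatment condition (active or placebo tDCS; active or placebo cognitive intervention) will be examined as a between-groups variable". It then plans follow-up tests without listing them: "comparisons using Bonferroni correction will be performed where appropriate". All secondary outcomes follow the same strategy. The Cox model for the follow-up phase also carries the randomised treatment as one group variable. The only interactions mentioned in the analysis text are those of risk factors in that follow-up analysis.

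**The concern.** A 2x2 factorial trial followed over time has three independent variables: tDCS, cognitive intervention and time. The article counts two. An analyst who follows the count would fit a four-level group factor crossed with time. A significant result would then show that the four groups do not change in the same way. It would not show which treatment is responsible, or whether the combination gives more than the sum of its parts.

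Two things are at stake. First, the planned primary test does not correspond to the factorial questions, so the contrast that carries the conclusion would be chosen after the data are seen. Second, the usual gain of a factorial design, that each treatment is assessed on all 100 patients as 50 v 50, is not secured by the stated plan.

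**Working it through.** **1. Counting terms.** With four groups and three time points, the group-by-time test has (4 - 1) x (3 - 1) = 6 degrees of freedom. In a tDCS by cognitive intervention by time model the same 6 split into three named parts of 2 each: tDCS-by-time, cognitive-by-time and tDCS-by-cognitive-by-time. The article specifies the undivided test only.

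**2. The protocol's own planning figure.** The Sample Size section gives 3.76 points, SD 1.32, p < 0.05, 90% power and at least 10 per group. The standardised effect is 3.76/1.32 = 2.85. The two-sample normal formula gives n = 2 x (1.96 + 1.28)^2 x (1.32/3.76)^2 = 2.6, so 3 per group; the exact t test gives 4. The stated 10 does not reproduce, which is a separate matter from this point. What matters here is that at 2.85 SD with 25 per cell, every analysis below has power near 100%.

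**3. Illustration at moderate effects.** The following are assumptions and are not in the document: a tDCS effect of 0.5 or 0.6 SD, two-sided alpha 0.05, no dropout, and a single change score in place of three time points, so that the four-group test has 3 df. From the document: 25 per cell, which gives 96 error df.

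- Noncentrality with a tDCS effect e and no cognitive effect: 25 x 4 x (e/2)^2 = 25e^2, which is 6.25 at 0.5 SD and 9.0 at 0.6 SD.
- Noncentrality with both treatments additive at e, for the 3-df test: 25 x 2e^2 = 50e^2, which is 12.5 and 18.0.
- Pair of cells, 25 v 25: two-sample t test with 48 df and SE = SD x sqrt(2/25).

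| Test | 0.5 SD | 0.6 SD |
|---|---|---|
| Main effect, 50 v 50, 1 df, alpha 0.05 | 70% | 84% |
| Main effect, alpha 0.025 | 59% | 76% |
| Four-group test, 3 df, tDCS effect only | 52% | 69% |
| Four-group test, 3 df, both treatments additive | 84% | 95% |
| One pair of cells, unadjusted | 41% | 55% |
| One pair of cells, alpha 0.05/6 | 18% | 28% |

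The last row assumes that all six pairs of four groups are corrected for. The article does not give the number or type of post hoc comparisons.

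**4. Detectable difference at 80% power, alpha 0.05 (normal approximation, 1.96 + 0.84 = 2.80).**

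- Main effect: sqrt(2/50) x 2.80 = 0.56 SD.
- Pair of cells, unadjusted: sqrt(2/25) x 2.80 = 0.79 SD.
- Pair of cells, corrected for six: sqrt(2/25) x (2.64 + 0.84) = 0.98 SD.
- Interaction, as a difference of differences: sqrt(4/25) x 2.80 = 1.12 SD.

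**The case against.** The strongest reply is that the parenthesis in the model description names both treatments, each with its two levels, rather than listing four groups. A loosely worded 2x2 structure may therefore have been meant. A four-level factor and a saturated 2x2 are also the same fitted model with the same residual, and main effects and interaction are contrasts within it. Both points stand. They mean that what is missing is the naming of the contrasts, and that a reader who infers that the factorial effects will never be tested goes further than the text allows. They do not remove the problem: the article counts one inter-group variable and then refers to a single between-groups variable again, so two different primary tests could be claimed from the same paragraph.

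A reader might also infer that the plan commits to six Bonferroni-corrected pairs. It does not; post hoc comparisons are made only where appropriate, and neither pairs nor a number is stated.

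Nor is it right that the stated model answers none of the trial's questions. The Abstract's comparison of the isolated treatments reads most directly as one single-treatment cell against the other, and the question of using the therapies alone or together also involves cell comparisons. A four-group analysis bears on those.

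Finally, the size of the power loss depends on the scenario. The omnibus test does well when both treatments work, and nothing is lost at the protocol's own effect size.

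**Conclusion.** The point holds as a mismatch between the stated primary model and the factorial design. As written, the model gives an omnibus four-group-by-time test, and the article specifies no test of the tDCS effect, the cognitive-intervention effect or their interaction. This does not depend on any effect size.

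The loss of power is illustrative only. If tDCS alone has an effect of 0.5 to 0.6 SD, the four-group test gives up about 15 to 18 percentage points against the 50 v 50 main effect at alpha 0.05 (70 - 52 = 18; 84 - 69 = 15), and about 7 points if the main effects are tested at 0.025 (59 - 52 = 7; 76 - 69 = 7). Single cell pairs do worse. There is no such loss if both treatments are active at that size, or if the effect is as large as the protocol assumes. The figures rest on one change score, no dropout and effect sizes that the document does not give.

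**What to change.** Restate the primary model as tDCS (two levels) by cognitive intervention (two levels) by time. Name tDCS-by-time and cognitive-by-time as the planned primary tests, and state how multiplicity across the two is handled. Report the tDCS-by-cognitive-by-time term with its confidence interval. Always show the four simple effects: each treatment in the presence and in the absence of the other. Keep Bonferroni-corrected cell comparisons as secondary, and say which ones they are. Apply the same structure to the secondary outcomes.

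The change is to analysis wording only; it adds no patients, visits or data. It has three costs. Splitting alpha lowers the main-effect power, for example from 84% to 76% at 0.6 SD. Main effects need care in interpretation if the interaction is large, which is why the simple effects should stand beside them. And the interaction reaches 80% power only at about 1.1 SD, so re-specification does not give the trial an adequate test of synergy; that term should be estimated rather than relied on for significance.
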